### Sample size

NEXAF is designed as a superiority trial comparing two parallel groups, exercise in addition to usual care and usual care only (control). The sample size is calculated for the two primary endpoints; the mean time in AF during the 12-month intervention, and the AFEQT sum score at 12 months.

For the mean time-in-AF over 12 months, a 50% relative between-group difference or more at 12 months is considered clinically relevant, translating to a 5 percentage points absolute difference at a baseline AF burden of 10%. We assume the SD to be smaller in the exercise group than the control group during the intervention period due to expected values closer to zero, in line with a recent, similar study with SDs for 4-week averages of around 10 in the exercise group and around 20 in the control group.^13^ Using these SDs, which are probably conservative for a 12-month average, 318 patients (159 in each group) are needed to have at least 80% power (with a significance level of 0.05) to detect a 5 percentage points difference in mean AF-time in exercise versus controls using a two-sample t-test.

For the AFEQT, a difference in sum score of ±5 or more has previously been identified as a clinically important change at the individual patient level.^26^ Previous studies from comparable patient groups have reported SDs of 15–20,^27^ and an SD of 18 is used for sample size calculation. The sample size for AFEQT is estimated by a simulation using 1000 iterations of a linear mixed-model analysis, assuming three data points per participant (baseline, 6 months and 12 months), a treatment effect of 5 points at both follow-up time points, an SD of 18 points and a correlation between repeated measures of 0.5. Based on these assumptions we estimate that 155 patients in each group give a power of 80% (significance level 0.05) to detect a 5-point difference at 12 months follow-up. From these calculations, a total of 320 patients (160 in each group) are considered sufficient.

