During the remaining study period, participants should maintain the exercise volume and habits attained. They have access to a personal eHealth platform provided by MIA Health AS. Each participant also has access to a contact person (coach) that monitor exercise status and progress, give advice and support throughout the intervention. A total of seven coaches have the main responsibility for exercise supervision. In addition to following a written protocol, the coaches have regular meetings to share experience and distribute information. The main communication channel between the patient and coach is through an App and management portal. For self-monitoring of exercise volume participants can opt to use a personalised PA metric called Activity Quotient (AQ, previously PAI) for guidance.^18^ AQ is automatically calculated in the App based on continuous heart rate measurements. By obtaining at least 100 weekly AQ equivalents, the participants are certain to have reached a volume and intensity of exercise aligned to the recommendations. They should also be able to mix and match their individual exercise sessions after personal preferences (type, intensity and frequency) and be aware of facilities and possibilities in their own community. They receive feedback and support through the App, and activity levels are monitored continuously. Patients are also offered monthly group-based exercise sessions. Participants who fall below recommended volume over time or are at risk of dropping out are given closer follow-up through the App or meetings with the aim to tailor goals/programme, motivate and/or identify causes of low adherence.

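### The total of 320 is two complete-data sample sizes rounded up, so the stated 80% power for AFEQT holds only if fewer than about 4–5% of patients lack a 12-month score

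*Protocol article*

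**What the plan says.** The Sample size section of the protocol article makes one calculation for each primary endpoint.

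- **Time in AF.** A two-sample t-test for a difference of 5 percentage points, using "SDs for 4-week averages of around 10 in the exercise group and around 20 in the control group", gives the statement that "318 patients (159 in each group) are needed to have at least 80% power". The article calls these standard deviations probably conservative for a 12-month average.
- **AFEQT.** A simulation of a linear mixed model (1000 iterations), "assuming three data points per participant (baseline, 6 months and 12 months"), with a 5-point effect at both follow-ups, SD 18 and correlation 0.5, gives 155 per group for 80% power.

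The section then concludes: "From these calculations, a total of 320 patients (160 in each group) are considered sufficient". Neither calculation includes a loss rate.

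Elsewhere the article allows that data may be lost. Under Exercise group, participants who "are at risk of dropping out are given closer follow-up". Under Time in AF, the monitor may be removed at the participant's request. Under Statistical analyses, the planned primary analysis of time in AF is an ANCOVA adjusted for baseline burden, centre and AF subtype, and AFEQT is analysed by a linear mixed model.

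**The concern.** The sizes of 159 and 155 per arm are numbers of patients with complete outcomes. The target of 160 per arm is presented as following directly from them, and it adds only 1 and 5 patients per arm. In an open-label trial with 12 months of follow-up and questionnaires sent out digitally, some 12-month AFEQT scores can be expected to be missing.

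The two endpoints are not equally exposed. The AFEQT calculation already takes credit for the mixed model, the correlation with baseline and all three time points, so its stated inputs contain no unused efficiency. The time-in-AF calculation uses a simpler test than the planned analysis and standard deviations that the authors consider conservative, so it has some slack of unknown size.

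What is at stake is interpretation. The article's Conclusion describes the trial as powered for both outcomes. A null AFEQT result would be read against 80% power, when the true figure on the trial's own assumptions could be several points lower.

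**Working it through.** **Inputs (Sample size section).** Time in AF: difference 5, SDs 10 and 20, α 0.05. The two-sided test reproduces the stated size; a one-sided test would need only 124 per arm by the normal approximation. AFEQT: difference 5, SD 18, correlation 0.5, α 0.05. The loss fraction d is **assumed** at 5–20%, since the article gives none.

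**Step 1: reproduce the stated sizes.**

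*Time in AF.* SE = √((10² + 20²)/n). At n = 159, SE = √(500/159) = 1.773 and 5/SE = 2.820. The Welch test (noncentral t, about 232 df) gives power 80.2%. At n = 158 it is 79.9%, so 159 is the smallest size that reaches 80%.

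*AFEQT.* Adjusting for baseline at correlation 0.5 leaves a residual variance of 18² × (1 − 0.5²) = 243, so SE = √(2 × 243/n). At n = 155, SE = √(486/155) = 1.771 and 5/SE = 2.824. Power = Φ(2.824 − 1.960) = 80.6%, or 80.4% with the t distribution. An unadjusted or change-score analysis would need 204 per arm, so the stated 155 does rely on the baseline correlation.

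Both stated sizes are confirmed as complete-data figures.

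**Step 2: the margin at 160 per arm.** Time in AF: (320 − 318)/320 = 0.6%. AFEQT: (320 − 310)/320 = 3.1%. With no loss, power is 80.4% and 81.8%.

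**Step 3: AFEQT with loss.** Patients with a 12-month score per arm: n = 160 × (1 − d).

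| d (assumed) | n per arm | 5/SE | Power, 12-month completers | Power if all lost after 6 months still give a 6-month score |
|---|---|---|---|---|
| 5% | 152 | 2.796 | 79.8% | 80.1% |
| 10% | 144 | 2.722 | 77.7% | 78.1% |
| 15% | 136 | 2.645 | 75.3% | 76.0% |
| 20% | 128 | 2.566 | 72.8% | 73.7% |

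The fourth column uses the normal approximation. The t distribution lowers it by about 0.3 points (77.4% at 10%, 72.5% at 20%). The last column is the most favourable case for the mixed model, and it adds at most about 1 point.

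The smallest n with 80% power is 153 (normal) or 154 (t). The tolerable loss is therefore 1 − 153/160 = 4.4% or 1 − 154/160 = 3.8%, rising to about 5% in the most favourable 6-month case.

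**Step 4: time in AF with loss.** The first power column is the t-test used for sizing. The other two approximate the planned ANCOVA by multiplying both SDs by √(1 − ρ²), where ρ is an **assumed** correlation between baseline and follow-up burden.

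| d (assumed) | t-test used for sizing | ANCOVA, ρ = 0.3 | ANCOVA, ρ = 0.5 |
|---|---|---|---|
| 5% | 78.4% | 82.1% | 88.7% |
| 10% | 76.1% | 80.0% | 87.0% |
| 15% | 73.7% | 77.6% | 85.0% |
| 20% | 71.1% | 75.1% | 82.8% |

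Smaller standard deviations work in the same direction. If both are 5% lower (9.5 and 19), even the t-test has 80.3% power at 10% loss. If both are 10% lower (9 and 18), it has 79.9% at 20% loss.

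**The case against.** The strongest reply is that nothing is miscalculated. Both sizes reproduce, and 320 complete patients do give the stated power. That stands: the point concerns an unstated assumption.

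A reader might infer that the design fails to deliver 80% power for both endpoints. The article does not support this. For time in AF the t-test appears only in the sizing, while the planned analysis is an ANCOVA. The article also says: "Using these SDs, which are probably conservative for a 12-month average, 318 patients (159 in each group) are needed". In addition, the outcome is a percentage recorded by an implanted monitor, so a patient who leaves early can still contribute monitored time. Together these may well cover realistic loss. They remain unquantified, so they neither prove adequate power nor allow a shortfall to be claimed.

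The evidence for loss is also modest. The remark about dropping out sits in the coaching text for the exercise arm and describes a mitigation. Under intention-to-treat, leaving the programme is not the same as a missing outcome. No rate is given, so every figure with loss is conditional.

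For AFEQT, 79.8% at 5% loss is in practice the stated 80%. The article's figure comes from 1000 simulations, with a 95% Monte Carlo margin of 1.96 × √(0.8 × 0.2/1000) = 2.5 points, and 77.7% at 10% loss lies inside it. However, simulation error affects only how precisely the article estimated its power. The decline with loss is systematic and is calculated directly above.

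Finally, the full protocol may treat attrition. The article nevertheless gives a full derivation and draws the sufficiency statement directly from it, and that printed inference is what needs qualifying.

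**Conclusion.** The point holds for AFEQT and only in part for time in AF.

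- **AFEQT.** On the article's own inputs, with 160 randomised per arm, 80% power holds only if loss of the 12-month score stays below about 4–5%. At an assumed 10% loss the shortfall is about 2 to 2.5 points, and at 20% about 6 to 7.5 points.
- **Time in AF.** No shortfall is shown. The sizing t-test would fall to 76% at 10% loss and 71% at 20%. The planned ANCOVA holds 80% at 10% loss with an assumed correlation of 0.3, and 83% at 20% loss with 0.5. Power for this endpoint rests on a cushion that the article does not quantify.

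These results assume equal loss in the two arms, loss unrelated to outcome, and 160 randomised per arm. The article does not report the number actually randomised.

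**What to change.** The Study design section says randomisation was concluded by October 2024, so the sample size should not be changed. In the Sample size section, replace the statement that 320 is sufficient with a short paragraph that:

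1. says that 318 and 310 are numbers with complete outcomes;
2. gives the number randomised and the expected or, if known, the observed proportion without a 12-month AFEQT score and without full monitor data;
3. gives AFEQT power under the planned mixed model at that loss, or over 5–20% if it is not yet known;
4. gives time-in-AF power under the planned ANCOVA, stating the baseline correlation and the 12-month SDs assumed, and how partial monitor time counts.

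The cost is one paragraph and a rerun of the existing simulation with missing 12-month scores. No patients are added and the analyses stay the same. The downside is a slightly less favourable stated AFEQT power. The stated power for time in AF may go up or down.

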### Dissemination

At a group level, we believe the general benefits of exercise outweigh potential risks also in patients with AF, although we cannot exclude an unfavourable effect on AF burden in individual patients. Review of medical journals and thorough testing at baseline, including maximal exercise testing with ECG, echocardiography and monitoring of heart rate and rhythm, should minimise the risk of adverse events. A safety monitoring board consisting of two experienced cardiologists and a statistician performed unblinded review of safety data after 100 participants had been included for at least 6 months. The results of the study will be submitted for publication in relevant international peer-reviewed journals and made publicly available through open access or self-archiving.

## Conclusion

The NEXAF trial is designed and powered to provide documentation of long-term exercise effects on total AF burden and disease-specific QoL. Its results may contribute to more specific guidelines on exercise in future AF management strategies.

## Data Availability

No data are available.
